**1. Declaration**

The study is conducted in strict accordance with the project plan and records the test data truthfully and accurately; there is no conflict of interest.

**2. Research title**

Renin-angiotensin system mechanism underlying the effect of auricular acupuncture on blood pressure in hypertensive patients with phlegm-dampness constitution

**3. Funding**

Zhejiang province scientific research fund project of traditional Chinese medicine (2022ZA053)

**4. Trial process chart**

| Outcomes | Evaluation time | | |
| --- | --- | --- | --- |
|  | Baseline | 4 weeks after allocation | 8 weeks after allocation |
| Blood pressure | × | × | × |
| phlegm-dampness constitution score | × | × | × |
| Proteins of the RAS | × |  | × |
| Gene polymorphism testing (only intervention group) | × |  |  |

**5. Background**

Essential Hypertension (EH) is a major contributor to the cardiovascular disease and premature death worldwide. It is also a serious disease that seriously endangers human health. Effective management of blood pressure is a key means to reduce the morbidity and mortality of chronic diseases such as coronary heart disease and stroke.EH is most prevalent among middle-aged and elderly individuals. Nearly half of Chinese people aged 35-75 years have EH; however, less than one-third receive treatment and less than one-twelfth have their blood pressure under control. Therefore, the prevention and treatment of EH in this group has become one of the important problems to be solved in the medical community today. Precision medicine proposed by Western medicine, also known as individualized treatment, helps patients, with the help of cutting-edge technologies such as genomic, proteomics determination and living environment, to develop optimal treatment plans for individual disease characteristics, in order to pursue the maximum treatment effect and the lowest side effects. This is similar to the idea of “preventivetreatment of disease” and the idea of “Dialectical treatment” in the traditional Chinese medicine (TCM) constitution.

**1. The TCM constitution is the expression of the basic elements of precision medicine, TCM constitution can be the “Chinese-style precision medicine”**

Emerging evidence indicates that EH is closely associated with the TCM constitution. The TCM constitution is a new branch of TCM; it plays an important role in analyzing the initiation, development, and prognosis of disease, and in guiding disease prevention and treatment. According to TCM principles, the TCM constitution depends on the intrinsic characteristics of the human body and is affected by the environment. There are nine constitution types including balanced constitution, qi-deficiency constitution, yang-deficiency constitution, yindeficiency constitution, phlegm-dampness constitution, dampness-heat constitution, blood stasis constitution, qi stagnation constitution, and inherited special constitution (balanced constitution is a normal constitution, and the other eight types are biased constitutions). Through analysis of the literature, we found that phlegm-dampness constitution (PDC) is one of the most common biased constitution in EH patients, with an incidence of 14.62% to 43.0%. A recent meta-analysis revealed that people with PDC were at considerable risk of developing hypertension. Therefore, intervention measures for EH patients with PDC are of great clinical significance.

**2. Compared with pharmacological treatment, TCM non-pharmacological treatment also plays an important role in the prevention and treatment of EH**

EH can be treated by both pharmacological and non-pharmacological approaches. Pharmacological trials have shown that only 25% to 62% of EH patients can reduce blood pressure and maintain it in the normal range by monotherapy, and most patients need more than one antihypertensive drug, which will increase the economic burden of patients and increase the risk of drug side effects. Therefore, choosing inexpensive, safe and easy to implement treatments is crucial for the prevention and treatment of hypertension. TCM non-pharmacological treatments are safe and easy, and only need short-term training, suitable for EH patients. As a time- and cost-efficient intervention that is relatively safe, auricular acupuncture might be a promising treatment option. TCM theory holds that diseases are caused by an imbalance in a person’s Qi and that the ears are directly or indirectly connected with the 12 meridians; thus, stimulating the corresponding acupoints in the ear can help to correct this imbalance. Auricular acupuncture restores the body to harmony in a gentle way and helps to solve health problems. Based on the characteristics of PDC and EH, the auricular acupuncture intervention scheme was formulated. To lower the blood pressure and improve the TCM constitution of EH patients with PDC can reflect the “Chinese-style precision medicine”. Numerous clinical studies have been performed to determine whether auricular acupuncture is beneficial for the treatment of hypertension. However, the mechanism underlying the hypotensive effect of auricular acupuncture still requires clarification.

**3. The RAS may be related to the mechanism of auricular acupuncture, The mechanism maybe involve ACE, AngⅡ, AT_1_R, ACE2, Ang (1-7), MasR**

The renin-angiotensin system (RAS) has been shown to play a pathophysiological role in the development and progression of EH. The classical RAS pathway is composed of angiotensin-converting enzyme (ACE), angiotensin Ⅱ (Ang Ⅱ), and angiotensin Ⅱ type 1 receptor (AT_1_R). In recent years, the new members of the RAS system, angiotensin-converting enzyme 2 (ACE2), angiotensin (1-7) [Ang (1-7)] and its receptor (MasR), constitute the new axis of RAS, namely, ACE2-Ang (1-7) -MasR axis.

**4. Genotypes may affect the sensitivity of EH patients with PDC to auricular acupuncture.**

By summarizing the existing clinical research literature, it have found that auricular acupuncture can reduce blood pressure and improve related symptoms, but some patients are not sensitive to auricular acupuncture in many researches. Furthermore, multiple studies have shown that antihypertensive drug efficacy is associated with the gene polymorphism of RAS. Huang Hong’s study showed that In EH patients with different genotypes of ACE gene, the antihypertensive efficacy of irbesartan and the reduction of plasma RAS activity before and after irbesartan treatment were different, manifested as DD > ID > II, which shows that the ACE I/D polymorphism may be an important indicator affecting the antihypertensive response to irbesartan in EH patients. Gong Hongtao using polymerase chain reaction to analyze AT_1_R genes 1166A/C, -810A/T and -521C/T polymorphism of the patients, The results showed a significant difference in the comparison of diastolic blood pressure drop before and after using telmisartan between the AT_1_R gene -521C/T CC genotype and CT + TT genotype (P<0.05), it showed that the -521C/T polymorphism of AT_1_R gene can independently predict the individual difference in patients' response to telmisartan. Men Chen investigated the relationship of A1675G gene polymorphism of AT_2_R and antihypertensive efficacy of losartan in EH patients, found that A allele may be the key factor influencing the antihypertensive efficacy of losartan. In conclusion, gene polymorphisms determine the differences in the effect of antihypertensive drugs, resulting in individual differences in the effect of drug treatment. Therefore, it is speculated that gene polymorphisms may also affect the effect of auricular acupuncture, but no relevant study has reported the relationship between the effect of EH and auricular acupuncture in patients with different genotypes. This study intends to test the polymorphisms of key genes of RAS in EH patients with PDC, analyze the sensitivity of different genotypes and alleles to auricular acupuncture, and provide a reference for improving the efficacy of auricular acupuncture.

**6. Research purposes**

(1) The changes of proteins of the RAS before and after auricular acupuncture will be compared to explore the mechanism underlying the effect of auricular acupuncture on blood pressure.

(2) Participants in the intervention group will have gene polymorphism testing, the changes in blood pressure of different genotypes will be analyzed to determine whether genotype influence the blood pressure-decreasing response to antihypertensive treatment with auricular acupuncture. And to identify genes of RAS that are sensitive to auricular acupuncture.

**7. Inclusion/Exclusion criteria**

**Inclusion criteria:**

- Individuals of both sexes, aged between 45 and 74 years;
- diagnosed with PDC;
- diagnosed with EH according to the diagnostic criteria of the International Society of Hypertension Global Hypertension Practice Guidelines.

**Exclusion criteria:**

- Individuals with mixed TCM constitutions;
- allergy to the medical devices involved in this trial;
- ear infections at the application sites during the course of the study;
- taking ACE inhibitors or angiotensin receptor blockers;
- poor medication compliance;
- the presence of serious complications such as severe arrhythmia or end-stage renal disease;
- pregnancy or lactation during the trial;
- history of mental disease;
- presence of malignant tumors;
- has received any other antihypertensive clinical test.

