**13. Safety assessment**

Although auricular acupuncture is typically regarded as a safe treatment, participants will be assessed for any discomfort. Details of all adverse events will be recorded during the trial in the case report forms (CRFs). The ethics committee will examine any connections between adverse events and the intervention and make a decision on whether the study should be continued.

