**17. Operational approach**

Participants will be seated and the skin on the auricular acupoints will be sterilized with a 75% alcohol swab. A sterilized XS100-A acupoint detector will be used to probe and mark each acupoint. An adhesive patch (0.5 cm*0.5 cm) with Wangbuliuxing seeds will be taped on the points. Well-trained and certified auricular therapists will instruct all participants to apply pressure to each auricular acupoint using their thumb and index finger until they feel pain and heat. Participants will be supported to self-perform acupressure 20 to 30 times on each auricular acupoint, three times daily. Auricular acupuncture will be carried out on the auricular acupoints on one ear in one visit and the opposite ear in the following visit. The adhesive patch will be replaced by the researcher every three days over the eight-week duration of the trial.

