**23. Treatment and management of the participants after the trial**

Participants in the control group who did not receive auricular acupuncture will be treated by a free 2-month auricular acupuncture service.

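### An exclusion criterion describes an ear infection that can arise only after randomisation and only in the treated arm, so applying it as written could exclude randomised participants from one arm

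*Protocol*

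**What the plan says.** The exclusion criteria in section 7 of the protocol include "ear infections at the application sites during the course of the study" and "pregnancy or lactation during the trial". Both are dated to the study period rather than to screening.

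Section 17 describes seed patches taped to auricular points: "The adhesive patch will be replaced by the researcher every three days over the eight-week duration of the trial". Section 23, on care after the trial, refers to "Participants in the control group who did not receive auricular acupuncture" and offers them the treatment afterwards.

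On harms, section 13 states: "Details of all adverse events will be recorded during the trial in the case report forms". It adds: "The ethics committee will examine any connections between adverse events and the intervention".

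The protocol has no separate withdrawal criteria. It does not say what happens to a randomised participant, or to that participant's data, when an exclusion criterion is met after allocation.

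**The concern.** An exclusion criterion should be answerable before allocation. An infection at a patch site during the study is not: no application site exists until treatment starts. The item therefore works, if it works at all, as a rule about people already randomised.

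It is also one-sided. Controls wear no patches, so they cannot meet it. Losing participants from one arm, for an event that the treatment itself may cause, is the kind of selection that randomisation is meant to prevent. The primary outcome is a response proportion with 40 planned per arm, so each person taken out of the denominator shifts the treated rate visibly.

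A SAP may well define the analysis sets, and their absence here is not the complaint. The complaint is that the eligibility text belongs to the protocol and makes a post-randomisation event a ground for exclusion. An analysis set defined later as all eligible participants would carry that exclusion into the primary comparison.

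**Working it through.** **Inputs.** From protocol section 9: planned response 28% versus 0%, α 0.05, β 0.10, dropout 20%, 40 per group. From section 18: chi-squared or Fisher's exact test for the response comparison. From sections 17 and 23: patches in the intervention arm only. Not given anywhere: an infection rate, or any relation between infection and response.

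**The plan's own figure.** With p̄ = (0.28 + 0)/2 = 0.14 and two-sided α, n = 2 × 0.14 × 0.86 × (1.960 + 1.282)² / 0.28² = 32.27 per group. Allowing for dropout, 32/0.8 = 40, and 33 × 1.2 = 39.6, which rounds to 40. Rounding 32.27 up first gives 33/0.8 = 41.25, so 42. The stated 40 reproduces to within 2 participants, and this point does not depend on it.

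**Timing and arm of each criterion.**

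| Criterion | Assessable at enrolment as worded? | Arm that can meet it |
|---|---|---|
| Ear infection at application sites | No | Intervention only |
| Pregnancy or lactation | In part: it can be present at enrolment, but the wording extends through the trial | Either |

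**How many cases.** With 40 treated and assumed infection rates of 2%, 5% and 10%, expected cases are 40 × 0.02 = 0.8, 40 × 0.05 = 2 and 40 × 0.10 = 4.

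**Effect on the treated response rate.** Assume 9 responders among 40. This is the planned 28% of the 32 expected completers: 0.28 × 32 = 8.96.

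| Removed from treated arm | All non-responders | Same response rate as the arm | All responders |
|---|---|---|---|
| 0 | 9/40 = 22.5% | 22.5% | 9/40 = 22.5% |
| 2 | 9/38 = 23.7% | 22.5% on average | 7/38 = 18.4% |
| 4 | 9/36 = 25.0% | 22.5% on average | 5/36 = 13.9% |

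Starting instead from 11/40 (27.5%, the nearest count to 28% of 40), removing 2 or 4 non-responders gives 11/38 = 28.9% or 11/36 = 30.6%.

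**Effect on the test.** With the planned 0% control response, 9/40 versus 0/40 already gives a two-sided Fisher p of 0.002, and removing non-responders only lowers it. A threshold crossing needs a different assumed result. For 8/40 versus 2/40 Fisher p = 0.087; with one treated non-responder removed (8/39) p = 0.048, and with two removed (8/38) p = 0.045. The uncorrected chi-squared p for 8/40 versus 2/40 is 0.043 before any removal, so that crossing is specific to Fisher's test.

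**The case against.** The strongest reply is that nobody is actually removed. The only stated uses of the criteria come before allocation: section 10 gives envelopes to eligible participants, and section 14 takes consent from those who meet the criteria. No removal or data-deletion rule exists. On that view the ear item is a clumsy way of describing infection at screening. This stands in part: the text supports that participants could be removed, not that they would be. But the item as worded has no meaning at screening, and nothing else in the protocol tells staff how to read it.

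Four stronger readings may tempt a reader, and the documents do not support them.

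- **That ear infections would vanish from the safety record.** Section 13 requires details of all adverse events during the trial to be recorded, and provides for review of any link with the intervention. It exempts neither ear infection nor people who leave.
- **That the exclusion list generally describes events after randomisation.** Only the ear item does so clearly. Pregnancy or lactation can be present at enrolment, is not tied to an arm, and is likely to be rare at ages 45 to 74. The item "poor medication compliance" carries no time wording and reads naturally as status before enrolment, so it is not part of this point.
- **That the bias must favour treatment.** Nothing in the protocol links a local ear infection to diastolic response. If the two are unrelated, removal does not change the expected rate.
- **That the whole 20% dropout allowance could be charged to this rule.** Removing 8 treated non-responders would turn 9/40 (22.5%) into 9/32 (28.1%). But section 9 gives that allowance for dropout during the research, without tying it to this rule or to one arm. The figure is an extreme case, not an estimate.

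**Conclusion.** The point holds in a limited form. The ear-infection criterion is misplaced: it describes a post-randomisation event that can fall only on the treated arm, and applying it as written could exclude randomised participants from that arm for a possible harm of the intervention. The pregnancy or lactation item shares the timing fault but not the one-sidedness.

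The size is not known from the documents. Assuming 9/40 responders and 2 or 4 removals, all of them non-responders, the treated rate rises by 1.2 or 2.5 percentage points. Other assumptions give no change on average, or a fall. At the planned rates the conclusion of the primary test would not change. It could change only with a closer result such as 8/40 versus 2/40 under Fisher's test. The protocol should be corrected because the change is cheap and protects the randomised comparison, not because a material bias has been shown.

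**What to change.** Reword both criteria in section 7 as status at enrolment: ear infection at the intended application sites at screening, and pregnant or lactating at screening. Add a sentence that these criteria are applied once, before randomisation, and that a randomised participant who later develops such an event stays in outcome follow-up and in the analysis by allocated group. State in section 13 that ear infection at an application site is reported as an adverse event, so that sections 7 and 13 agree. Whether treatment is stopped in such a case is a clinical decision for the sponsor and is outside this point.

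The cost is a wording amendment, with no change to sample size or visits. The possible downside is a slightly less favourable efficacy rate, if those retained turn out to be non-responders.

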**8. Study design**

Randomized controlled trial, parallel

[figure not shown]

**9. Sample size calculation**

The sample size for this RCT has been computed based on our previous study (36). In our previous study, the efficacy rate was 28% in the intervention group and 0% in the control group after eight weeks of auricular acupuncture intervention. Setting an α-value of 0.05 and a β-value of 0.10, the sample size was calculated using the following formula:

$$n=\frac{{2\bar{p}\bar{q}\left( z_{\alpha}+z_{\beta} \right)}^{2}}{\left( p_{1}-p_{2} \right)^{2}}$$

Considering a dropout rate of 20% during the research, a total of 40 participants per group will be enrolled in the study, for a total required sample size of 80.

**10. Randomization**

A statistician will generate a random sequence using SPSS 25.0 software and the random sequence will be placed in opaque envelopes. Eligible participants will receive an envelope in the order of enrollment and will deliver this to the auricular therapist. The researcher who sealed the random sequence envelopes will not take part in the inclusion, treatment, or evaluation of the participants.

**11. Blinding**

The participants will be treated individually, and the assessor and the statistician will be blinded to the group allocation.

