**12. Outcomes**

**Main outcome**

**Efficacy of auricular acupuncture:** The blood pressure will be measured at baseline, 4 weeks and 8 weeks after allocation. The efficacy of auricular acupuncture is defined as office diastolic blood pressure is reduced to a threshold set out in “Guiding Principles for Clinical Research of New Chinese Medicines” formulated by the Ministry of Health of the Peoples Republic of China a significant effect means a diastolic blood pressure decrease ≥10 mmHg and return to normal level or a decrease ≥ 20 mmHg. An effect means a diastolic blood pressure decrease <10 mmHg and return to normal level or decrease of 10 to 20 mmHg. Invalid means that the change in blood pressure did not reach the “effect” level described above.

Requirements for blood pressure measurement:

(1) blood pressure will be measured in the afternoon and in a quiet room with comfortable temperature (22℃-24℃) by one well-trained researcher.

(2) use validated upper-arm cuff device and sphygmomanometer for blood pressure measurement, and ensure the calibration before the measurement.

(3) Before measurements: remain seated and relaxed for at least 5 min; avoid smoking, caffeine and exercise for 30 min; empty bladder.

(4) Sit in a backrest chair with back supported on chair, legs uncrossed and feet flat on floor, arm resting on table with mid-arm at heart level.

(5) Tie the cuff to the upper arm, and tighten it so that it can be inserted 1 to 2 fingers. The lower edge of the cuff should be 2.5cm above the elbow fossa.

(6) Blood pressure of both upper arms is measured at first visit and the higher side is usually measured later. At each visit take 2 measurements with 1-2 min between them. Calculate the average of the 2 measurements. If the 2 readings of systolic or diastolic blood pressure varied by more than 10mmHg, the third time is taken and the average of the last two measurements is recorded.

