**18. Statistical analysis**

The statistician will use SPSS 25.0 software to analyze the data; a *P*-value < 0.05 will be considered statistically significant. Continuous variables will be expressed as means and standard deviations, or as medians and interquartile ranges. Categorical variables will be expressed as frequencies. Continuous variables will be analyzed by *t* tests or Wilcoxon rank-sum tests. The difference before and after treatment in each group will be determined using a paired *t* test. A chi-squared or Fisher’s exact test will be used to compare the efficiency between the intervention and control groups.

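### Blinding of assessor and statistician is promised, but the procedures expose allocation to the assessor at weeks 4 and 8 and do not secure the statistician's blinding

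*Protocol*

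**What the plan says.** Section 11 (Blinding) says that participants are treated individually and that "the assessor and the statistician will be blinded to the group allocation". It gives no procedure.

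The sections that bear on this are:

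- **Section 17 (Operational approach).** "An adhesive patch (0.5 cm*0.5 cm) with Wangbuliuxing seeds will be taped on the points". The ears alternate from visit to visit. "The adhesive patch will be replaced by the researcher every three days", for the eight weeks of the trial.
- **Section 23.** Controls are described as not having had auricular acupuncture, and are offered it free after the trial.
- **Section 12 (Main outcome).** Blood pressure is measured at baseline, week 4 and week 8 "by one well-trained researcher". Response is judged from diastolic pressure thresholds.
- **Section 12 (Secondary outcomes).** TCM physicians determine the PDC score at the same three time points. Only the intervention group is genotyped, as the chart in section 4 also shows.
- **Section 10 (Randomization).** "A statistician will generate a random sequence using SPSS 25.0 software". The only rule separating roles is this: "The researcher who sealed the random sequence envelopes will not take part in the inclusion, treatment, or evaluation of the participants".
- **Section 18 (Statistical analysis).** "The statistician will use SPSS 25.0 software to analyze the data".

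**The concern.** The blinding statement is a positive claim that readers of the trial report will rely on. The participants cannot be blind to wearing patches, so blinded assessment is the main protection left for the outcomes.

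The primary outcome is a category cut from an in-person reading. A participant counts as a responder if diastolic pressure falls into the normal range, or falls by at least 10 mmHg. Near those limits, a small shift in how readings are taken in one arm moves people from non-responder to responder. The PDC score involves a rater and is open to the same influence.

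Blinding of the statistician matters for choices made after the data are seen, such as handling of dropouts or choosing between a t test and a rank-sum test. If the analyst knows the arms, those choices are not protected.

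**Working it through.** The protocol gives no figure for the effect of unblinding, so there is none to reproduce. The check is to follow the procedures as written and see who could learn the allocation, and when.

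1. **When patches are worn.** Assume treatment starts at allocation. Eight weeks is 8 × 7 = 56 days, and renewal every three days gives 56 ÷ 3 ≈ 18.7 intervals, so wear is close to continuous. The week 4 reading falls on day 4 × 7 = 28, in the middle of this period. The week 8 reading falls on day 56, at its end. The text does not say whether patches come off before that reading. The baseline reading precedes treatment, so nothing is visible then.

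2. **Whether the arms look different.** Section 17 describes seed patches. Section 23 says controls had no auricular acupuncture, and no sham patch appears in the text. A patch on the ear therefore identifies the intervention arm.

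3. **Whether the assessor can see it.** Section 12 sets out six measurement requirements, covering room, device, rest, posture, cuff and repeat readings. The participant sits with the reader. None of the six covers the ears or removes the patches. The protocol describes no masking for the PDC rating either.

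4. **Whether the assessor could also be treating.** Section 17 gives patch renewal to a researcher, and section 12 gives blood pressure to a researcher. No sentence makes these different people. The separation rule in section 10 covers only the person who sealed the envelopes.

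5. **Whether the statistician is separated.** Section 10 has a statistician create the sequence, and sections 11 and 18 have the statistician blinded and analysing. The text does not say whether this is one person or two. The bar in section 10 covers inclusion, treatment and evaluation. It does not mention analysis and applies to the envelope sealer.

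6. **Whether the data themselves reveal the arm.** Genotype is collected in the intervention group only. In a combined dataset, a filled genotype field means intervention and an empty one means control (missing samples aside). Coding the arms A and B does not help while those fields are present.

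7. **Whether the size can be derived.** The number of participants that a given reading shift would turn into responders depends on the diastolic mean and SD, the value taken as normal, and the size of the shift. The protocol gives none of these. Section 9 gives only response rates of 28% and 0%, which do not determine them. If very few controls respond, as the 0% suggests, few may lie close to a threshold and the effect could be small. If many lie close to the normal limit, it could be material.

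**The case against.** The strongest case on the other side has four parts.

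- **Visibility is inferred.** No sentence says that the assessor sees the patches, and the design figure in section 8 is not available, so a control procedure shown there cannot be excluded. This stands as a caution. But the text describes patches in one arm, an in-person reading and no covering, and visibility is what follows from doing as written.
- **Roles may be separate in practice.** Sections 10 and 17 refer to auricular therapists, and section 11 names an assessor, which suggests different people. A reader might infer that one researcher both renews patches and measures pressure, or that one statistician both makes the sequence and analyses. The documents support neither. They show only that the roles are not kept apart.
- **Measurement is already standardised.** Section 12 requires a validated, calibrated device, rest, set posture, averaged duplicate readings and a rule for a third. These limit careless or erratic readings and deserve credit. They do not hide the allocation, and nothing requires automated or stored readings.
- **Coded analysis is often left to the analysis plan.** That is fair for the coding itself. It does not excuse an unconditional promise of a blinded statistician beside one-arm genotype data, with no mention of withholding them.

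**Conclusion.** The point holds. Followed as written, the procedures do not deliver a blinded assessor at weeks 4 and 8, for blood pressure or for the PDC score, and they do not secure a blinded statistician. The assessor part is the firmer. It rests on controls wearing no patch, on patches being in place at the visit (clear at week 4, not stated for week 8) and on no masking step in the missing figure. The genotype part is also firm if the analyst receives the full dataset. The statistician part is a gap in role separation and does not show that blinding is broken.

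Two wider conclusions are tempting and should not be drawn. One is that every blood pressure reading is unblinded; the baseline reading is not affected. The other is that the false-positive rate or the response rate rises by a particular amount. Any such figure would need an assumed diastolic distribution and an assumed reading bias, neither of which is in the protocol. A figure based on covariance analysis would also concern a test that section 18 does not plan. The direction of the risk is clear, but its size is unknown. It should be corrected because the remedy is cheap and the primary outcome depends on it.

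**What to change.** - Before the week 4 and week 8 assessments, existing staff other than the assessor cover both ears of every participant in both arms with a cap or headband. Both ears are needed because the treated side alternates, and both arms because a covering in one arm would itself reveal allocation.
- State that the blood pressure assessor and the PDC raters never apply or replace patches.
- Have the sequence generated and held by someone who takes no part in the analysis, and say so. Handing this to the envelope sealer is not enough by itself, because the present bar on that person does not extend to analysis.
- Analyse the primary outcome under coded arms, with genotype data withheld until that analysis is final. The genotype comparisons lie within the intervention arm and can wait.
- If these steps are not taken, withdraw the blinding statement and report the trial as open-label with unblinded assessment.

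The cost is caps or headbands, a few sentences on roles and a data-release step, with no extra staff for the covering. The remaining weakness is that participants may tell the assessor which arm they are in.
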